### Reporting of adverse events

Due to the nature of the registry, immediate reporting of AEs and serious AEs to the local EC/IRB is not required, unless indicated otherwise by the local EC/IRB. The occurrence of AEs and severe AEs will be summarized in annual reports and submitted to the EC/IRB, as required.

### Statistical analyses

As the registry aims are mainly descriptive and exploratory, patient characteristics and outcomes recorded at the standard of care scheduled FU assessments will be presented using simple summary statistics. Categorical variables will be summarized using the frequency and percentage for each category. Continuous variables will be summarized using the mean, standard deviation, median, interquartile range, and the minimum and maximum values. Additionally, summary statistics will be presented and stratified to clinically relevant categories, including the type of treatment received. Complications will be reported at both the patient and AE levels. Multiple events of the same type will be combined for each patient. Upon calculating complication rates, the denominator will be the total population size, irrespective of dropouts during FU. All complication rates will be presented with 95% confidence intervals. In addition to overall rates, complications will be presented according to categories for various relevant parameters, such as “action taken” (none/operative/nonoperative) or “outcome” (in progress/without persistent damage/with persistent damage/death). Patients with more than one event of the same type will be presented according to the most severe category.

To identify risk factors and evaluate specific research questions, it is planned to perform further appropriate statistics (e.g., multivariable analyses) if the volume and quantity of the collected data allows this. Enrolled patients who withdraw from the study FU for any reason (withdrawal of consent, death, loss to FU, etc.) will be included in the analysis until the time at which they withdrew.

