#### Interventions and study procedures

Patients will undergo fracture fixation using osteosynthesis, including single- or multiple-staged procedures (e.g., initial external fixation with later conversion to internal fixation). The operative treatment for TSFs in adults mainly depends on the fracture characteristics and extent of the soft tissue damage and is to be performed according to the standard (routine) care procedures based on the individual clinician’s judgment and patient characteristics. Neither specific treatment nor specific time points for FU visits are dictated for registry purposes.

Registry-related assessments will include radiographic evaluations, performed by the treating surgeon at the treatment visit and at defined time points after treatment, following each site’s standard (routine) visit schedule for up to 36 months. Radiographic images and/or clinical pictures will be stored to enable future ad-hoc analysis after de-identification. If patients are unable to attend the last planned FU visit, they will be contacted by e-mail or phone to document the final outcomes, especially patient-reported outcomes (PROs) and complications not previously captured. The planned registry schedule is displayed in Table 2 over the 36-months FU visit period.

**Table 2 Tab2:** Registry schedule for the Fracture-Related Outcome Study for operatively treated Tibia shaft fractures (F.R.O.S.T.)

	Baseline	Treatment	Post-treatment visit 1^a^	Post-treatment visit 2^a^	Post-treatment visit 3^a^	Additional Post-treatment visit(s)^a^
	–	Day 0	6 weeks (target 42 days: range 14 to 105)	6 months (target 183 days; range 106 to 260)	12 months (target 365 days, range 261 to 456)	Up to 36 months
Eligibility	X					
Patient information/consent	X^b^					
Demographics	X					
Medical history and pre-treatment values	X					
Injury(s) details	X					
Treatment details		X^c^				
Clinical outcome(s)			X	X	X	X
Patient-reported outcome(s)						
PROMIS: Global Health	X		X	X	X	X
PROMIS: Physical Function	X		X	X	X	X
PROMIS: Pain Interference			X	X	X	X
Pain numeric rating scale (NRS)			X	X	X	X
Complications			X	X	X	X
Images and/or other clinical pictures	X^d^	X^d^	X^d^	X^d^	X^d^	X^d^

^a^ If a patient does not visit at the specified time point, the visits will be assigned according to the specified rules. Additional postoperative visits may take place up to 36 months after day 0

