### Outcome measures

The data collected in this registry will include treatment details, clinical outcomes, PROs, and procedure- or implant-related AEs. Documentation of treatment details will comprise information about the time from injury to index surgery, duration of surgery, number of stages of the procedure, skin preparation, tourniquet use, details about debridement and irrigation, type of reduction/fixation method, specifics related to the fixation devices (e.g., material type, implant dimension*)*, intraoperative blood loss, as well as the use of local agents to promote bone healing. Moreover, information relating to the perioperative use of either prophylactic or curative systemic antibiotics and application of local antimicrobials will be documented and entered in the database. Furthermore, information pertaining to soft-tissue management will be recorded, such as timing and details of wound closure, soft-tissue coverage, and flap type. For concomitant fractures of the tibia or fibula, the treatment method will be documented. If further treatments are performed during the index surgery, these will also be captured.

Clinical outcome documentation will include time to bone healing/union, the presence of malalignment, malrotation or malunion, and the time to full weight bearing. Time to bone healing is defined as the time elapsed between definitive treatment and bony union. The healing status assessment will be based on a combination of clinical and radiological parameters, which will be judged by the treating surgeon. Clinically, healing will be rated as complete when the patient is able to walk without support in the absence of pain or tenderness at the fracture site. Radiologically, the modified RUST score [18] will be determined by scoring each cortex on the anteroposterior (AP) and lateral radiographs as 1 = no callus, 2 = callus present, 3 = bridging callus, and 4 = remodeled, fracture not visible. The modified RUST score is the sum of these and therefore has a value from 4 to 16.

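### The only stated summary rule that fits time to bone healing and time to full weight bearing is mean/SD/median of observed values, which leaves out patients without the event and, for healing, is likely to carry each site's visit schedule into the result

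*Protocol article*

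**What the plan says.** In the protocol article, Statistical analyses sets the general rule: "patient characteristics and outcomes recorded at the standard of care scheduled FU assessments will be presented using simple summary statistics". Categorical variables get counts and percentages. For the rest, "Continuous variables will be summarized using the mean, standard deviation, median, interquartile range, and the minimum and maximum values". The same section adds that "summary statistics will be presented and stratified to clinically relevant categories, including the type of treatment received". Complications have rules of their own; times to an event have none.

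Outcome measures lists time to union first among the clinical outcomes: "Time to bone healing is defined as the time elapsed between definitive treatment and bony union". On how union is established it says: "The healing status assessment will be based on a combination of clinical and radiological parameters, which will be judged by the treating surgeon". Time to full weight bearing runs from definitive treatment to the point at which the surgeon permits it.

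On visits, Interventions and study procedures states: "Neither specific treatment nor specific time points for FU visits are dictated for registry purposes". Table 2 assigns visits to windows of 14–105, 106–260 and 261–456 days, with further visits possible up to 36 months.

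Two other statements bear on the point. Patients who leave follow-up for any reason "will be included in the analysis until the time at which they withdrew". Nonunion, and inability to bear full weight one year after definitive treatment, are pre-defined complications.

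**The concern.** Both outcomes are times to an event that some patients never reach while under observation. A mean and SD need a number for every patient counted, so two problems arise.

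1. **Patients without the event have no value.** The summary becomes time among those seen to heal. A treatment after which more fractures fail to unite need not look slower. The rule also does not fit the sentence on withdrawals: a mean cannot include a patient up to a date, whereas a censored analysis can.

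2. **Union is seen only at a visit.** It is known to lie between the last visit without union and the first visit with it. If the later date is recorded, the time is too long by an amount that depends on the local schedule.

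The Discussion gives the registry's main purpose as relating treatment strategies to outcomes, and Table 1 lists 12 current and 5 planned sites. Treatment and visit timing both follow local practice. Where the two go together, a schedule effect could be read as a difference in healing speed.

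**Working it through.** The article has no figure of its own to reproduce here. The check asks what the stated summary returns when true healing is known.

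**Inputs from the article.** Nonunion c = 3% to 17% (Background); about 1000 patients (Sample size estimation); visit targets 42/183/365 days and the window edges (Table 2).

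**Assumptions not in the article.** Healing times among healers are Weibull with shape 2 and median m = 150 days (120 and 180 also tried), the same at every site. There is no dropout. Union is dated at the first visit where it is seen. Schedule B below is an invented denser routine.

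**Formulas.** Among healers, F(t) = 1 − 2^(−(t/m)²). For visits v₁ < … < v_K, the probability that union is first seen at visit k is p_k = F(v_k) − F(v_(k−1)), with F(v₀) = 0.
- Share of patients with a value = (1 − c) × F(v_K)
- Mean of recorded times = Σ v_k p_k / F(v_K)

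The factor (1 − c) cancels from the mean. With equal healing speed among healers, the nonunion rate therefore cannot affect it.

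**Schedule A (42/183/365), m = 150.** F = 0.0529, 0.6436, 0.9835, so p = 0.0529, 0.5907, 0.3399. The mean is (2.22 + 108.10 + 124.07)/0.9835 ≈ 238 days. The true mean among healers is 150/√(ln 2) × Γ(1.5) ≈ 160 days.

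**Schedule B (42/91/137/183/274/365).** p = 0.0529, 0.1723, 0.2139, 0.2045, 0.2574, 0.0825. The mean is 185.27/0.9835 ≈ 188 days.

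| Schedule, days (m = 150) | Mean | Median | Share with a value, c = 3% | c = 17% |
|---|---|---|---|---|
| A: 42/183/365 (targets) | 238 | 183 | 95% | 82% |
| B: six visits, as above | 188 | 183 | 95% | 82% |
| C: 14/106/261 (early edges) | 209 | 261 | 85% | 73% |
| D: 105/260/456 (late edges) | 239 | 260 | 97% | 83% |

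**Nonunion.** 0.03 × 1000 = 30 and 0.17 × 1000 = 170 patients have no time. On schedule B both groups give a mean of 188 and a median of 183 days. Healers not yet seen to unite by the last visit are lost as well; under C that leaves 85% or 73% with a value.

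**Schedule.** Healing is identical in every row.
- A minus B is 51, 50 and 48 days at m = 120, 150 and 180.
- D minus B is 47, 51 and 59 days.
- With shape 2.2 and m = 150, schedule A against seven visits (42/84/126/168/210/270/365) gives 238.5 − 180.6 = 58 days.

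Not every pair differs this much: A and D are about one day apart in the mean, although their medians are 183 and 260.

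**What a better analysis returns.** The true median over all patients is m√(−log₂(1 − 0.5/(1 − c))), which is 153 days at c = 3% and 173 at c = 17%. In simulated data with 20,000 patients per scenario, an interval-censored Weibull model with a never-healing fraction gave 153–154 and 172–174 days across all four schedules. That model matches the one used to generate the data, so good recovery is expected. Kaplan–Meier using visit dates keeps the non-healers but gave medians of 183, 183, 261 and 260 days for A to D, so it does not remove the schedule effect.

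**The case against.** The strongest reply is that the article never says these two times will be given as mean and SD. It states a generic rule, its withdrawal sentence reads like censoring, and it leaves room for further analyses such as multivariable ones. It is also a condensed account of a protocol not shown, and the choice of estimator often sits in an analysis plan. This stands as far as it goes: the application to the two times is an inference. But the section covers outcomes in general, states one rule for quantities of this kind and makes no exception. That is a stated rule that does not fit, rather than a detail left for later.

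A reader might infer that non-healers vanish from the report. They do not. Nonunion and inability to bear full weight at one year are reported as complications with 95% confidence intervals. That limits the harm but does not correct the time summary. Those rates also use the total population whatever the dropout, so patients lost before diagnosis count as free of the event.

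A reader might also carry the visit-schedule argument over to weight bearing. The article does not support that. The endpoint there is the surgeon's permission, a dated act. Only the missing-value problem applies to it, and no figure above concerns it.

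Finally, no site's actual schedule is given. The Table 2 windows assign visits to time points and do not show that assessments are months apart.

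**Conclusion.** The point holds in limited form, at moderate severity. Read as written, the summary rule leaves patients without the event out of both time outcomes. It also hides differences in nonunion within the healing-time summary, and it sits badly with the sentence on withdrawals. For bone healing, the recorded time is likely to reflect when patients were seen.

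The exclusion of about 30–170 per 1000 follows from the article's own nonunion range. The roughly 50–60 day gap rests on assumed Weibull healing times, assumed schedules and dating union by visit, so it illustrates the possible size and is not a forecast.

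It would go too far to conclude that treatment comparisons will be biased. That requires schedules to differ between the groups compared, which the article makes possible but does not show. Nor is this a fatal fault: the registry is mainly descriptive and exploratory, and the remedy lies in the analysis.

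**What to change.** Exempt both times from the mean/SD rule.

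- **Time to union:** analyse as interval-censored, from the last visit without union to the first visit with it, right-censored at last contact, with death as a competing event. Report the proportion united at 6 and 12 months and the median over all patients. Use an interval-censored model for comparisons.
- **Time to full weight bearing:** use the date of permission as the event date, right-censor patients without it at last contact, and report Kaplan–Meier or cumulative incidence estimates.
- **Withdrawals:** say that the sentence on inclusion until withdrawal means censoring at that time for these two outcomes.

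The cost is wording, standard software and slightly more analysis. Table 2 already schedules clinical outcomes at every post-treatment visit, so no new data should be needed, provided the case report form holds visit dates, healing status at each visit and the date of permission. The downside is that estimates will look less precise where visits are sparse. At time points that fall between visits, they will lean on the model or on patients seen at other times.

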### Procedures

#### Recruitment

First, the investigator or another appropriately trained member of the research team at the study site identifies all eligible patients. These patients should meet all inclusion criteria and none of the exclusion criteria. Next, they inquire about the patient’s interest in participating in this study. If the patient wishes to participate, a legally eligible member of the research team goes through the informed consent process with the patient, explaining the study’s purpose, procedures, risk/benefits, alternatives to participation, and data protection. Each patient who chooses to participate signs and dates an ICF*.* All consenting patients are allocated a unique patient trial number. A protocol deviation is documented for patients found ineligible after treatment, indicating which inclusion/exclusion criterion (or criteria) was (or were) violated.

The follow-up (FU) population will consist of patients who have signed informed consent, are eligible (i.e., meet all inclusion and none of the exclusion criteria), and have commenced treatment (i.e., definitive treatment). Recruitment is planned to take 36 months to enroll a minimum of 1000 patients. An evaluation will take place at the end of this period. If deemed necessary, due to a high percentage of dropouts for example, the study period may be extended.

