### Premature termination

Due to the nature of the registry, no stopping rules have been defined. All treatments will be per standard of care, and no additional or investigational medical device or medication will be administered during the investigation. Patient participation in the study may end prematurely for one of the following reasons:
The patient withdraws informed consentScreening failure (patient not meeting the eligibility criteria)Investigator’s discretion (e.g., patient noncompliance with the registry plan)Sponsor’s decisionUnknown/lost to FUDeath

In the case of premature termination, detailed information explaining the circumstances leading to termination will be obtained and recorded in the eCRF.

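### The fixed denominator for complication rates treats time lost to follow-up as event-free, so rates of follow-up-dependent complications are lower bounds

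*Protocol article*

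**What the plan says.** All references are to the protocol article.

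- **Statistical analyses, numerator.** Complications are counted per patient and per event. At patient level, "Multiple events of the same type will be combined for each patient".
- **Statistical analyses, denominator and interval.** For complication rates, "the denominator will be the total population size, irrespective of dropouts during FU". Then: "All complication rates will be presented with 95% confidence intervals". The section also plans summaries stratified by treatment received.
- **Statistical analyses, last sentence.** Patients who leave follow-up for any reason, death included, "will be included in the analysis until the time at which they withdrew".
- **Recruitment.** "The follow-up (FU) population will consist of patients who have signed informed consent, are eligible", and must have started definitive treatment. "Recruitment is planned to take 36 months to enroll a minimum of 1000 patients". On loss, the text says only that, "due to a high percentage of dropouts for example, the study period may be extended". No dropout rate is given.
- **Length of follow-up.** The Abstract gives a minimum of 12 months. Interventions and study procedures allows up to 36 months on each site's routine schedule. Patients who cannot attend the last planned visit are to be reached by e-mail or phone, partly to pick up complications not yet recorded.
- **Outcome measures.** The pre-defined postoperative complications include FRI, nonunion, refracture and not being able to bear full weight at one year. A start date is recorded for each event.

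**The concern.** The denominator rule is a stated choice, not a detail left to a later document. A patient who leaves follow-up without a recorded complication contributes a full unit to the denominator and nothing to the numerator, whatever happens afterwards.

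The effect is largest for complications diagnosed late. Full weight bearing at one year is the clearest case: it cannot be known for a patient lost before one year, yet under the rule that patient counts as not having the problem.

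Two uses of the rates are at risk. First, the descriptive rates with confidence intervals are a main output of the registry, and readers will take them as estimates of how often these complications occur. Second, the Discussion gives the registry's main purpose as relating treatment strategy to outcome. If one treatment group or type of site loses more patients, its complication rate falls for that reason alone.

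**Working it through.** The article has no dropout, power or precision figure to reproduce, so the check asks how far the rule can move a rate.

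**Inputs**
- N = 1000, the enrolment minimum in Recruitment.
- True cumulative incidence p: nonunion 3% to 17%, FRI 1% (closed low-energy fractures) to 25–30% (complex open fractures), all from Background.
- d, the share of patients lost: not given; assumed 10%, 20% or 30%.
- f, the share of lost patients' events that fall after loss: assumed 0.5 or 1.
- Loss is assumed independent of outcome, with no events recovered by phone or e-mail.

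**Formula.** Lost patients would have d × p × N events, of which a share f goes unrecorded. The expected reported rate is

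q = p × (1 − d × f),

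so the relative bias is −d × f. Coverage is the exact binomial probability that a Wilson 95% interval, calculated on a count with mean 1000 × q, contains p.

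**Results for N = 1000**

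| True rate p | Loss d | f | Reported q | 95% CI at q | Coverage of p |
|---|---|---|---|---|---|
| 17% | 0 | – | 17.0% | 14.8–19.5% | 95% |
| 17% | 10% | 1 | 15.3% | 13.2–17.7% | 71% |
| 17% | 20% | 0.5 | 15.3% | 13.2–17.7% | 71% |
| 17% | 20% | 1 | 13.6% | 11.6–15.9% | 17% |
| 17% | 30% | 1 | 11.9% | 10.0–14.1% | 0.4% |
| 3% | 20% | 1 | 2.4% | 1.6–3.6% | 82% |
| 1% | 20% | 1 | 0.8% | 0.4–1.6% | 95.5% |

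Example, fourth row: 0.17 × (1 − 0.20 × 1) = 0.136.

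For FRI at 25%, 20% loss with f = 1 gives 0.25 × 0.80 = 20.0%. Coverage at N = 1000 is not quoted, because complex open fractures will be only part of the registry.

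**Strata.** Take two groups with the same true rate of 10%, one losing 10% and the other 30%.
- f = 1: 0.10 × 0.90 = 9.0% against 0.10 × 0.70 = 7.0%, a spurious ratio of 9.0/7.0 = 1.29.
- f = 0.5: 0.10 × 0.95 = 9.5% against 0.10 × 0.85 = 8.5%, a ratio of 1.12.

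**After correction.** With p = 17%, 20% loss and f = 1, dividing by patients actually followed gives 136/800 = 17.0% (95% CI 14.6–19.8%). The rule as written gives 136/1000 = 13.6% (11.6–15.9%). A cumulative incidence estimate would also use the partial follow-up of those lost.

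**The case against.** The strongest defence is that the registry is descriptive and exploratory, the crude proportion is a transparent summary, and its interval is valid for what it literally measures: the proportion of patients with a recorded complication. The phone or e-mail contact will recover some missed events. The alternative has its own assumption: if patients who are doing well stop attending, a censored estimate will be too high and the crude proportion may be nearer the truth.

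Much of this stands. It limits the size of the problem and means the censoring assumption must be stated. It does not remove the defect, since patients who withdraw or cannot be reached are still scored as event-free, and nothing labels the result a lower bound.

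A reader might also infer several stronger claims that the document does not support:

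- *Every lost patient counts as complication-free.* A complication recorded before loss stays in the numerator; only later, unobserved events are missed.
- *Every rate is biased.* Intraoperative complications do not depend on follow-up. Keeping patients who die in the denominator is also right for a cumulative incidence with death as a competing event.
- *The intervals are invalid.* That depends on a dropout rate the article does not give. With little loss, or a rate near 1%, coverage stays close to 95%.
- *The divisor is everyone enrolled.* The rule does not define its population. Recruitment describes a follow-up population of consented, eligible patients who have begun definitive treatment.
- *The section contradicts itself.* Saying that withdrawn patients "will be included in the analysis until the time at which they withdrew" may mean only that their data up to withdrawal are kept. It is ambiguous for complication rates, not a proven conflict.
- *Patients seen for 12 months are scored event-free to 36 months.* No 36-month complication rate is stated.
- *Ending participation for "patient noncompliance with the registry plan" adds outcome-related loss.* This is given only as an example of investigator discretion, and nothing in the text shows that such loss is related to outcome.

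**Conclusion.** The concern holds for postoperative complications that need follow-up to be detected. For these, a proportion over the whole population cannot exceed what complete follow-up would have shown. That direction does not depend on why patients were lost; the size does.

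Under non-informative loss the shortfall is a fraction d × f of the true rate: 10% to 20% of it at 20% loss, for f between 0.5 and 1. Whether the interval misleads depends on how common the complication is. Coverage is seriously reduced at the top of the quoted nonunion range and little changed near 1%. Comparisons between treatment strata are distorted wherever loss differs.

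The dropout rates, the values of f and the independence of loss from outcome are assumptions made here, and events recovered by phone or e-mail would shrink every figure.

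**What to change.** Replace the denominator sentence for postoperative complications with wording to this effect:

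> Postoperative complications are reported as cumulative incidence at 12 months, and later where follow-up allows, from definitive treatment to the first event of each type. Patients are censored at last contact and death is a competing event (Aalen-Johansen). Estimates are given with 95% confidence intervals and numbers at risk. Outcomes defined by status at a fixed time, such as full weight bearing at one year, use patients assessed at that time as the denominator.

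In addition:
- Keep the crude proportion if wanted, labelled as a lower bound, and name the population it is divided by. It can remain the main summary for intraoperative complications.
- State that the censored estimates assume loss unrelated to outcome, and show the amount of loss by treatment stratum.
- Say how the sentence on including withdrawn patients up to withdrawal applies to complication rates.

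The cost is small: revised wording and a little more analysis. Event start dates and the circumstances of early termination are already collected. Reported rates will be somewhat higher with wider intervals, and they will rest on the censoring assumption.
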